## **7 STUDY OBJECTIVES**

### **7.1 PRIMARY OBJECTIVE**

Evaluation of maximal tolerable dose of MaaT033 in patients with AML or HR-MSD

### **7.2 SECONDARY OBJECTIVES**

Evaluation of overall safety

Dose regimen evaluation: identification of a recommended phase II dose (RP2D) based on gut microbiota engraftment

### **7.3 EXPLORATORY OBJECTIVES**

- Assessment of a microbiota signature
- Impact of our full ecosystem intestinal microbiota biotherapeutic (MaaT033) on the immune system

Corresponding endpoints are detailed in § section [8.3](#).

|                                                                                   |                    |                                                                      |
|-----------------------------------------------------------------------------------|--------------------|----------------------------------------------------------------------|
| [figure not shown] | DOCUMENT    | Protocol ID : MPOH05
EudraCT N° : 2019-004253-89
Version: 10.0 |
|                                                                                   | CIMON STUDY | Date : 04 MAY 2021
Page 23 / 70                                   |

## 8 INVESTIGATIONAL PLAN

### 8.1 TYPE OF TRIAL

Interventional phase I trial

### 8.2 STUDY DESIGN

#### 8.2.1 **Methodology and study phases**

Open-label, single-arm phase 1 study to evaluate the safety of MaaT033 in a step-up dosing design from 2 capsules 7 days apart to 9 capsules per day for 7 days.

Choice of cohort is based on the definition of maximum and minimum dose regimen acceptable for good compliance. 1 capsule per week is a reasonable minimum dosing while 9 capsules per day is a maximum we could define for such a population, already having quite important medications.

Our target dose is also in between these 2 cohorts, with 3 capsules per day. We decided to assess the impact of treatment duration with the comparison between a 7 days courses versus 14 days.

The study has the following phases:

- **Patient pre-screening phase** - Patients diagnosed with hematologic malignancy will be asked if they are willing to participate in this study by the investigating physician and will sign the informed consent form before any study examination. Only patients with neutropenia recovery will be finally included in the study.  
Neutropenia recovery is defined as a level of Absolute Neutrophil Count (ANC)  $\geq 0.5 \times 10^9$  cells/L.
- **Treatment phase** - The treatment will be started within 2 days after patient's inclusion. Clinical evaluation will be performed at baseline, at the interim visit (day7), before new cycle of chemotherapy start if any (day19 if not) and after new cycle chemotherapy if any (day44 if not). A step-up process will be applied between 5 different cohorts of patients and will depend on patient's tolerance of the treatment.
- **Follow-up phase:**  
Patient's overall status will be evaluated at D44 post inclusion (V4).  
AE/SAE collection will be performed from time of informed consent to V4.

#### 8.2.2 **Decision rules for choice of dose regimen**

This study has for objective to assess MTD and MAD in term of MaaT033 activity (bacteria engraftment). Activity assessment requires a minimum of 6 patients to allow for a sufficient robust analysis of engraftment.

Activity and tolerability assessment may depend both on duration of treatment and/or daily dose. Therefore, the study will assess both 7 days and 14 days dose regimen, for the 3 capsules/day dosing.

Therefore, the study will ensure that a minimum of 6 patients is included for all the dose regimen that do not reach the MTD.

Definitions:

**Minimal Active Dose (MAD):** Minimum dose regimen that will lead to a minimal activity (1 or 2, cf chapter 8.3.2) of the product.

|                                                                                   |                    |                                                                      |
|-----------------------------------------------------------------------------------|--------------------|----------------------------------------------------------------------|
| [figure not shown] | DOCUMENT    | Protocol ID : MPOH05
EudraCT N° : 2019-004253-89
Version: 10.0 |
|                                                                                   | CIMON STUDY | Date : 04 MAY 2021
Page 24 / 70                                   |

**Dose Limiting Toxicity (DLT):** Toxicity event will be defined as any related adverse event grade >3 based on CTCAE v5.0 criteria for:

- Blood and lymphatic system disorders (DLT when grade4 or 5)
- Immune system disorders (DLT when grade4 or 5)

And any related adverse event grade  $\geq 3$  for all other system organ.

**Maximal Tolerated Dose (MTD):** Maximal dose for which only 0 or 1 patient do experience limiting toxicity out of a cohort of 6 patients.

The study has an adapted “6 dose titration” escalation design to allow for assessment of tolerability (research of the Maximal Tolerated Dose) and of activity (research of Minimal Active Dose):

- **1st level of dose for 1st cohort:** - 3 Patients will be treated with one capsule/day on day 1 and D7. The Safety Committee (SC) will evaluate occurrence of Limiting Toxicity after the 3 patients will have completed V3. If no patient experiments a DLT, the following cohort will use dose level 2 *i.e.* 1 capsule/Day for 7 days. If one or more patient experiment a DLT, the SC might consider study stop recommendation or cohort continuation. The purpose of this cohort is to assess feasibility of the whole procedure and check any unexpected tolerability issue that would prohibit continuation of the experimentation. As the dose schedule is not considered as sufficient enough to allow for any effective activity, it will not be considered for the choice of final dose.
- **2nd Level of dose (cohort2):** 6 patients will be treated with 1 capsule/day for 7 days. The Safety Committee (SC) will evaluate occurrence of Limiting Toxicity after the 6 patients will have completed V3. If no or 1 patient experiments a DLT, the following cohort will use dose level 3 *i.e.* 3 capsules/day for 7 days. If two or more patients out of 6 experiment a DLT, the study will be stopped.
- **3rd level of dose (cohort3):** 6 patients will be treated with 3 capsules/day for 7 days. The Safety Committee (SC) will evaluate occurrence of Limiting Toxicity after the 6 patients will have completed V3. If no or 1 patient experiments a DLT, the following cohort will use dose level 4 *i.e.* 3 capsules/D for 14 days and dose level 5 *i.e.* 9 capsules/day for 7 days. If two or more patients out of 6 experiment a DLT, the study will be stopped.
- **4th level of dose:** 6 patients will be treated with 3 capsules/day for 14 days. The Safety Committee (SC) will evaluate occurrence of Limiting Toxicity after the 6 patients will have completed V3. If no or 1 patient experiments a DLT, the following cohort will use dose level 5 *i.e.* 9 capsules/day for 7 days. If two or more patients out of 6 experiment a DLT, the study will be stopped. Of note, if 2 or more DLT are reported during the 7 first days of treatment, then the SC will re-assess cohort3 evaluation.
- **5th level of dose:** 6 patients will be treated with 9 capsules/day for 7 days. The Safety Committee (SC) will evaluate occurrence of Limiting Toxicity after the 6 patients will have completed V3. If two patients or more experiment a DLT, the study will be stopped and MTD will be considered as dose level 4. If one patient or less experiments a DLT, the MTD will be considered dose level 5.

**In any of the cohort 2 to 5, if any safety signal suggesting potential DLT is reported in 2 or more patient before the end of the inclusion of all patient of the cohort, inclusion of subsequent patient will be suspended and ad hoc meeting of the DSMB will be hold with all available information to assess those potential DLT and decide on the continuation or stopping the study.**

**A 24-hour gap should be respected between inclusions of the first 3 patients of each cohort to consider potential early or delayed toxicities.**

|                                                                                   |                    |                                                                      |
|-----------------------------------------------------------------------------------|--------------------|----------------------------------------------------------------------|
| [figure not shown] | DOCUMENT    | Protocol ID : MPOH05
EudraCT N° : 2019-004253-89
Version: 10.0 |
|                                                                                   | CIMON STUDY | Date : 04 MAY 2021
Page 25 / 70                                   |

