### **12.1.3.2 Serious Adverse Events**

In the case of a Serious Adverse Event the Investigator must immediately:

- 1 ENTER (within 24 hours) the information related to the Serious Adverse Event in the appropriate screens of the e-CRF; the system will automatically send the notification to the pharmacovigilance officer after approval of the Investigator within the e-CRF or after a standard delay. A back-up plan is in place (using paper flow) when the e-CRF system does not work,
- 2 In case of eCRF system failure, FILL in (within 24 hours) the information related to the Serious Adverse Event in the appropriate Serious Adverse Event Form and fax it immediately to the pharmacovigilance officer (Vigipharm subcontractor).
- 3 SEND (preferably by fax or e-mail) the photocopy of all examinations carried out and the dates on which these examinations were performed, to the pharmacovigilance officer.

Care should be taken to ensure that the subject's identity is protected and the subject's identifiers in the Clinical Trial are properly mentioned on any copy of source document provided to the Sponsor. For laboratory results, include the laboratory normal ranges.

All further data updates should be recorded in the eCRF as appropriate, and further documentation as well as additional information (for lab data, concomitant medication, subject status) should be sent (by fax or e-mail) to the Monitoring Team within 24 hours of knowledge. In addition, any effort should be made to further document each Serious Adverse Event that is fatal or life threatening within the week (7 days) following initial notification.

SAE EMAIL : [[contact]](mailto:[contact])

SAE FAX N° [contact]

The Investigator must comply with any applicable site-specific requirements related to the reporting of SAEs) involving his/her subjects to the Ethics Committee/Institutional Review Board (EC/IRB) that approved the trial.

Investigator should ensure that adequate medical care is provided to the subject for any adverse event.

All SAE must be followed until the subject has recovered, stabilized, recovered with sequelae or died. The Investigator must forward follow-up information on SAE to MaaT Pharma within 5 days this information is obtained. SAE Follow-up report should be faxed accordingly to SAE EMAIL: [[contact]](mailto:[contact]) and SAE FAX N° [contact]

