#### **12.1.4.1 Tolerability consideration:**

Investigators will be trained regarding the mode of action of the investigational medicinal product and to be particularly attentive to any signs of toxicity.

**Dose Limiting Toxicity (DLT):** Based on the literature and our preclinical data, no particular toxicity is expected. Toxicity events will be defined as any at least possibly related adverse event grade  $\geq 3$  based on CTCAE v5.0 criteria. Due to the specific therapeutic protocol that blood cancer patients usually follow, the follow-up of patients in term of DLT is set from V1 (end of neutropenia) to V3 (start of a new chemotherapy cycle, or consolidation). Nevertheless, there are some anatomical or physiological system events that will be considered as expected in the context of patients with AML or HR-MSD, and thus not related to the treatment. Such events will only be considered DLT when grade  $> 3$ :

- Blood and lymphatic system disorders (DLT when grade 4 or 5)
- Immune system disorders (DLT when grade 4 or 5)

Depending on the number of DLTs, the dose is either escalated (0 DLTs) or de-escalated ( $\geq 2$  DLTs). Due to our specific drug activity assessment goals, cohorts 2 to 5 will systematically be expanded with 3 extra patients (0 or 1 DLTs) each.

|                                                                                   |                    |                                                                      |
|-----------------------------------------------------------------------------------|--------------------|----------------------------------------------------------------------|
| [figure not shown] | DOCUMENT    | Protocol ID : MPOH05
EudraCT N° : 2019-004253-89
Version: 10.0 |
|                                                                                   | CIMON STUDY | Date : 04 MAY 2021
Page 49 / 70                                   |

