#### **12.1.4.2 Cohort Review Meetings:**

**Ad-hoc meetings can be called at any moment if needed for Safety consideration (DSMB).**

The dose-escalation process will be monitored by a **cohort review committee (DSMB, see corresponding chapter 8.2.2. for the dose escalation rules)**.

A cohort review meeting will be organized once all patients at a specific dose level have completed the V1 to V3 DLT period to decide regarding dose escalation. A cohort review meeting will also be organized as soon as DLTs are observed in 2 or more patients to decide about stopping the dose escalation and confirming the Maximum Tolerated Dose (MTD) has been reached:

Cohort1: 3 first patients in this cohort will allow the assessment of a potential unexpected safety signal and will confirm feasibility of the procedure. The CRC will review patients after treatment completion of the 3 patients. Safety, tolerability and DLT events between V1 and V2 will be evaluated to take the decision on dose escalation.

Cohorts 2&3: These cohorts present a more classical posology (daily treatment of 1 and 3 capsules respectively) in the microbiome capsule category (see section introduction). The CRC will review patient tolerability after treatment completion of the 6 patients of the evaluated cohort, completed with follow up information from of the previous cohorts. Tolerability and DLT events between V1 and V3 will be evaluated to take the decision on dose escalation.

Cohorts 4&5: No more dose regimen escalation are expected. Tolerability of those patients will of course be closely monitored. Because cohort4 will first be completed, a SC will validate the step up to cohort5.

The focus of this meeting will be to review the overall patients' safety and to ensure all DLTs have been identified to decide escalation to the next dose level, or to confirm if the MTD has been reached.

At the time of the decision to escalate the dose, the cohort review committee may recommend one or more of the following with the aim of establishing an MTD and/or enhancing potential safety and tolerability:

- That additional medication is used
- That specific measures are taken in the treatment of side effects based on AEs and building upon the cumulated experience in their management
- That caution is exercised in patients presenting with conditions that may exacerbate any observed toxicities

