#### 13.3.2 **Responsibilities**

The Investigator or authorized designee is responsible for the timeliness, completeness, and accuracy of all observations and other data pertinent to the clinical investigation in the eCRFs. The Investigator will ensure that all data are entered promptly (within 4 days) after the evaluation has occurred, in accordance with source documents and specific instructions accompanying the eCRFs, designed specifically for the study. The Data Management Department of Eurofins Optimed will provide all tools, instructions, and training necessary to complete the eCRF, and each user will be issued a unique username and password. The data management of Eurofins Optimed will be responsible for data processing, in accordance with the CRO data management procedures.

|                                                                                   |                    |                                                                      |
|-----------------------------------------------------------------------------------|--------------------|----------------------------------------------------------------------|
| [figure not shown] | DOCUMENT    | Protocol ID : MPOH05
EudraCT N° : 2019-004253-89
Version: 10.0 |
|                                                                                   | CIMON STUDY | Date : 04 MAY 2021
Page 51 / 70                                   |

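### Suspension of inclusion turns on reported DLTs, but the 24-hour reporting route covers only serious events and pregnancy, so a non-serious DLT can reach the sponsor up to 3 days later than a serious one

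*Protocol*

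**What the plan says.** **The trigger.** Protocol 8.2.2 makes the rule for cohorts 2 to 5 act "if any safety signal suggesting potential DLT is reported in 2 or more patient before the end of the inclusion" of all patients of the cohort; then "inclusion of subsequent patient will be suspended and ad hoc meeting of the DSMB will be hold". Section 12.1.4.2 restates it: "A cohort review meeting will also be organized as soon as DLTs are observed in 2 or more patients".

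**The event.** Section 8.2.2 gives the definition as "Toxicity event will be defined as any related adverse event grade" above 3 for blood and immune disorders, and 3 or higher for all other organ systems. Section 12.1.4.1 has the same grades with slightly different wording on causality: "Toxicity events will be defined as any at least possibly related adverse event grade" 3 or higher, with the same two exceptions. Neither uses seriousness, and 12.1.3.6 points out that severe and serious are different things.

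**The reporting clocks.** For SAEs, 12.1.3.2 tells the investigator to "ENTER (within 24 hours) the information related to the Serious Adverse Event" and describes an automatic notification to the pharmacovigilance officer. For all other adverse events, 12.1.3.1 asks for recording in the eCRF and sets no notification time. The general rule in 13.3.2 then applies: "The Investigator will ensure that all data are entered promptly (within 4 days) after the evaluation has occurred".

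**Spacing.** Section 8.2.2 requires 24 hours between inclusions of the first three patients of each cohort. Nothing is stated for patients 4 to 6.

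**The concern.** The suspension rule can act only on what has been reported, yet the speed of reporting is tied to a different property of the event from the one that makes it a DLT. The count of two also has to be pooled over the 3 to 4 sites planned in the synopsis, and no provision lets one site see another's non-serious events as they arise. Two sites can each have one non-serious DLT, both comply with every stated deadline, and a further patient can still be included and treated at the same dose level. That is the situation the rule is meant to prevent.

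The protocol can expedite a non-serious event when it chooses. Section 12.1.3.10 puts pregnancy on the 24-hour route whether or not it is serious, and 12.1.2 makes every COVID-19 infection an SAE. The events that drive suspension have no equivalent.

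**Working it through.** The plan states no figure for reporting delay, so there is none to reproduce. The check sets the clocks side by side and then sizes the gap with the protocol's own accrual.

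**Step 1: clocks for an event that meets the DLT definition**

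| Event | Stated route | Stated limit | Alert described |
|---|---|---|---|
| DLT that is also an SAE | 12.1.3.2 | 24 hours | Yes, automatic |
| DLT that is not an SAE | 12.1.3.1 with 13.3.2 | 4 days after evaluation | None |

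Difference between the stated limits: 4 − 1 = 3 days.

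**Step 2: accrual.** Inputs: 27 patients (synopsis and 9.3; 3 + 4 × 6 = 27) and an inclusion period of 5 to 7 months (synopsis). Taking 30.44 days per month:
- 5 months: 27 / 152.2 = 0.177 per day
- 7 months: 27 / 213.1 = 0.127 per day

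**Step 3: expected inclusions in the extra 3 days, even accrual** (rate × 3)
- 0.177 × 3 = 0.53
- 0.127 × 3 = 0.38

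Treating inclusions as Poisson, the chance of at least one is 1 − exp(−0.53) = 41% and 1 − exp(−0.38) = 32%.

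**Step 4: allowing for pauses between cohorts.** Each cohort waits for review of the previous one after V3. Assume four pauses of 19 days (V3 at D19), 76 days in all:
- 5 months: 27 / (152.2 − 76) = 0.354 per day; × 3 = 1.06
- 7 months: 27 / (213.1 − 76) = 0.197 per day; × 3 = 0.59

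The chance of at least one is then 65% and 45%.

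**Step 5: upper limit.** If the second DLT is in the k-th patient of a cohort of 6, at most 6 − k patients remain to be included: four if k = 2.

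**Step 6: context only.** With X ~ Bin(6, p), P(X ≥ 2) = 1 − (1 − p)^6 − 6p(1 − p)^5. The rates are assumptions; the protocol gives none.

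| Assumed DLT rate | P(2 or more DLTs in 6) |
|---|---|
| 5% | 3% |
| 10% | 11% |
| 20% | 34% |
| 33% | 64% |

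This counts DLTs of every kind, serious ones included, so it does not measure the gap.

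**The case against.** The best case against the point is that the affected set is small. For events with no CTCAE term, 12.1.3.6 describes grade 3 by hospitalisation or invasive intervention and grade 4 as life-threatening or disabling, so these will largely be SAEs. The medically important criterion in 12.1.1 catches more, and 12.1.3.4 restricts which laboratory values count as adverse events. This stands: what remains is mainly related grade 3 events without hospitalisation and some grade 4 laboratory events.

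There are also safeguards. Section 12 asks investigators to consider an SAE form where necessary, 12.1.4.1 has them trained to watch for toxicity, and 12.1.4.2 allows an ad hoc meeting at any time. Section 8.2.2 does not say that a report means eCRF entry, and a DSMB charter or safety manual, not shown, may set a route. These soften the point without closing the gap: the SAE form is discretionary and untimed, and a meeting called at once still depends on the sponsor knowing. Section 6.4 lists one related SAE in 81 patients given earlier products, but that count omits non-serious events.

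A reader might infer more than the text supports:
- **A delay of 4 days.** The SAE route itself takes up to one day, so the excess is 3.
- **Events heard at the D2 call stop at source documents.** Section 11.1.4 asks for source documentation, but 12.1.3.1 still requires every adverse event from V1 to V4 in the eCRF.
- **The 5-day limit for SAE follow-up is a second gap.** That limit ("The Investigator must forward follow-up information on SAE to MaaT Pharma within 5 days this information is obtained") names the sponsor, while the 24-hour limit for additional information in the same section names the monitoring team. Because 8.2.2 acts on potential DLTs, an event already sent as an SAE can count on first report, so the 5 days matter little here.
- **The chance of two DLTs in a cohort is the share of cohorts harmed.** The gap also needs those DLTs to be non-serious, the second to arise while inclusion is open, and another patient to be included in the extra days.

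**Conclusion.** The mismatch is real and visible in the text: the trigger is defined by grade and relatedness, the expedited route by seriousness. Followed exactly, the stated clocks let inclusion continue after two non-serious DLTs at different sites.

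The effect is modest: up to 3 days beyond the SAE clock, about 0.4 to 0.5 further inclusions on average at even accrual, and 0.6 to 1.1 if inclusion pauses 19 days between cohorts. These figures apply only when the second non-serious DLT arises while patients remain to be included, and they treat the 4-day entry limit as the time to notification. The protocol does not say when anyone reviews such entries, so the real delay could be shorter or longer. The share of DLTs that are non-serious is not in the document; if it were nil, nothing would be lost. The change is still worth making, because it protects patients at little cost.

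**What to change.** In 12.1.3.2, add that any adverse event of DLT grade judged at least possibly related, serious or not, from V1 to V3, is entered and notified to the pharmacovigilance officer within 24 hours by the existing SAE route, and that the number of affected patients is kept across sites. In 8.2.2 and 12.1.4.2, refer to this notification as the report that triggers suspension and the review meeting.

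No dose, DLT grade or stopping threshold changes. At even accrual, expected inclusions within the stated reporting limit for a non-serious DLT fall from 0.51–0.71 (4 days) to 0.13–0.18 (1 day). The cost is protocol wording, an eCRF alert and a few more expedited entries for sites.
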